**Figure 2 figure2:**
[figure not shown]
Preoperative clinic value stream map. Blue blocks with maize writing indicate the main steps in the clinic process, whereas maize blocks with blue writing summarize tasks performed by the study coordinator. APP: advanced practice providers; GAD-7: Generalized Anxiety Disorder 7-item scale; KCCQ-12: Kansas City Cardiomyopathy Questionnaire 12-item short-form; PHQ-9: Patient Health Questionnaire-9; TATUM: Treatment Assignment Tool-University of Michigan.

### The Comfort Coach Approach and Interventions

In this trial, the *comfort coach* is a trained Certified Child Life Specialist who provides therapeutic interventions that have been shown to reduce anxiety and pain medication use while increasing patient and family satisfaction [15]. Child life specialists use evidence-based nonpharmacological pain management techniques such as preparing patients for painful encounters, comforting and reassuring them, coping strategies such as distraction, and offering positive reinforcement to support patients undergoing painful procedures [55]. These interventions focus on improving patient experience, validating emotions, and offering an individualized approach with the goal of reducing pain and anxiety. Focused breathing and guided imagery with targeted relaxation and pain management outcomes will support patient choice and engagement to encourage sustainable coping skills.

Child life specialists are trained in lifespan development and family systems theories, specifically addressing pain and anxiety through individualized comfort techniques. Though they are trained specifically in pediatrics, these coping strategies translate across ages. Adults routinely express the desire for distraction techniques, guided imagery, and preparation procedures during procedural care [16,23]. Moreover, adults may benefit, similar to pediatric patients, from nonpharmacological interventions when undergoing cardiac surgery. Whereas adults may have more experience with anxiety and pain management than children, new perioperative experiences have the potential to raise anxiety levels that can be mitigated by simple comfort strategies. Thus, child life specialists are ideally equipped to address perioperative anxiety and painful situations in both children and adults. We performed an 11-patient feasibility study in patients who underwent open cardiac surgery at Michigan Medicine using certified child life specialists, which demonstrated that nonpharmacological comfort coach interventions were feasible.

In this study, patients randomized to the intervention group will meet the comfort coach in the preoperative clinic (#1), where the coach will perform an introductory emotional, medical, and psychosocial needs assessment to consider the impact of surgery on the patient. The comfort coach will also introduce a *comfort menu* (Multimedia Appendix 1) [56-63] for pain management. After the preoperative clinic visit, the comfort coach will see the patient 5 additional times: at the preoperative bay immediately before surgery (#2), at extubation in the intensive care unit (**#**3), at chest tube removal (#4), at discharge (#5), and at the 30-day clinic follow-up visit (#6). These points of intervention were defined through feedback provided during our initial 11-patient feasibility study. During these intervention points, patients will receive the comfort menu and choose individualized interventions, including guided imagery, guided visualization, focused breathing, distraction techniques, music, art, mindfulness, and patient positioning. Supplies used during comfort coach interventions commonly include music playlists, compassion cards, stress balls, iPad activities, and virtual reality goggles. Additional activities are listed in the comfort menu in Multimedia Appendix 1.

### Study Overview and Pretrial CONSORT (Consolidated Standards of Reporting Trials) Flow Diagram

Screening, enrollment, randomization, and study design are summarized in Figure 3.

**Figure 3 figure3:**
[figure not shown]
Clinical trial CONSORT (Consolidated Standards of Reporting Trials) diagram. Patient population and clinical trial flow diagram. The timing of each *comfort coach* intervention touchpoint is indicated, and each touchpoint is numbered. BPI: Brief Pain Inventory; GAD-7: Generalized Anxiety Disorder 7-item scale; IES-R: Impact of Events Scale-Revised; KCCQ-12: Kansas City Cardiomyopathy Questionnaire 12-item short-form; PHQ-9: Patient Health Questionnaire-9.

#### Aim 1: Assess the Effect of a Comfort Coach on Patient Experience

To address this aim, we will examine the effect of the comfort coach on perioperative anxiety, self-reported pain, functional status, and patient satisfaction. We will use the Generalized Anxiety Disorder 7-item scale (GAD-7) [56] anxiety assessment and Patient Health Questionnaire-9 (PHQ-9) [57] depression scale at 4 points: preoperative clinic visit, discharge, and at 30- and 90-day follow-up. The Kansas City Cardiomyopathy Questionnaire short-form (KCCQ-12) [58,59] will be administered at the preoperative clinic visit and 30-day follow-up to evaluate functional status. The Impact of Events Scale-Revised (IES-R) [60] will measure event-related psychological stress at 30-day follow-up, and the Picker Patient Experience Questionnaire [61] will be administered at the 30-day follow-up. The Brief Pain Inventory [62,63] will be administered at discharge to assess in-hospital pain. We hypothesize that patients who receive a comfort coach report a better hospital experience, improved functional recovery, and lower levels of depression, anxiety, stress, and pain.

##### Outcome Measures for Aim 1

Outcome measures for aim 1 exclusively consist of validated measures for anxiety, depression, stress, pain, and patient satisfaction (Textbox 1). These validated tools were adapted to better evaluate differences in pharmacological and nonpharmacological treatments and their corresponding effects and are included in the Multimedia Appendix 1.

Evaluative surveys and questionnaires.Generalized Anxiety Disorder 7-item ScaleA 7-item validated questionnaire to assess and potentially diagnose generalized anxiety disorder [56].Patient Health QuestionnaireA 9-item validated questionnaire which generates a total score out of 27 used to diagnose 5 different degrees of depressive disorders [57].Impact of Events Scale-RevisedA 22-item validated scale used to measure event-related stress with the potential to indicate clinical suspicion or diagnosis of posttraumatic stress disorder [60].Picker Patient Experience QuestionnaireA 15-item questionnaire designed to capture the patient’s inpatient experience [61].Brief Pain InventoryShort-form 9-question inventory assessing patient pain location, severity, relief, and activity level [62,63].Postoperative Opioid and Pain Management QuestionnaireAn 11-item questionnaire developed at Michigan Medicine for collecting data on opioids prescribed, opioids used, pain scores, opioid storage and disposal practices, and assessment of opioid education.Kansas City Cardiomyopathy QuestionnaireA 12-item questionnaire assessing the impact of heart failure on the patient’s daily activities and lifestyle [58,59].

The survey and questionnaire instruments were used as part of specific aim #1 to evaluate anxiety (Generalized Anxiety Disorder 7-item scale [GAD-7]), depression (PHQ-9), functional status (Kansas City Cardiomyopathy Questionnaire short-form [KCCQ-12]), stress (Impact of Events Scale-Revised [IES-R]), and patient experience (Picker Patient). Patient-reported pain levels (BPI) and postdischarge opioid use and pain management practices (Postoperative Opioid and Pain Management Questionnaire [OPIOID]) were collected as part of specific aim #2.

##### Analytic Approach

Mean total GAD-7 and PHQ-9 scores at each of the 4 time-points (Table 1) will be compared between the 2 groups with two-tailed *t* tests, whereas categorical findings (eg, mild, moderate, or severe anxiety on the GAD-7 and minimal, mild, moderate, moderately severe, or severe depression on the PHQ-9) will be compared between groups using chi-square tests. In addition, repeated measures ANOVA (analysis of variance) tests will be performed for the GAD-7 and PHQ-9 across the 4 time-points to examine differences between groups while accounting for correlation over time within each patient. IES-R mean total scores will be compared between groups using a two-tailed *t* test, and the proportion of patients in each group meeting established cutoffs (≥24, ≥33, and ≥37) [64-66] will be compared with chi-square or Fisher exact tests, as appropriate. Chi-square tests will be used for the Picker Patient Experience Questionnaire to determine differences in mean proportions of *problems* reported out of the 15 items in the survey. The mean intrapatient difference between preoperative clinic and 30-day follow-up in functional status scores on the KCCQ-12 will be evaluated (≥5 point difference indicates a clinically important difference) and compared between study cohorts. Pain severity and pain interference scores will be determined (both out of 10) from the Brief Pain Inventory and generated for each patient. These 2 mean scores will be compared between groups using a two-tailed *t* test. Finally, pain score proportions on a 4-point scale (none, minimal, moderate, or severe) recorded through the 30-day postoperative questionnaire will be compared across groups using the chi-square test.

**Table 1 table1:** Schedule of survey instrument administration. The survey administration schedule is indicated for both study cohorts (ie, all patients).

Preoperative clinic visit for History and Physical	Day of discharge	30-day postoperative clinic visit	90-day postoperative clinic visit or phone call
GAD-7^a^	GAD-7	GAD-7	GAD-7
PHQ-9^b^	PHQ-9	PHQ-9	PHQ-9
KCCQ-12^c^	BPI^d^	Picker Patient^e^	N/A^f^
N/A	N/A	IES-R^g^	N/A
N/A	N/A	OPIOID^h^	N/A
N/A	N/A	KCCQ-12	N/A

^a^GAD-7: Generalized Anxiety Disorder 7-item scale.

^b^PHQ-9: Patient Health Questionnaire-9.

^c^KCCQ-12: Kansas City Cardiomyopathy Questionnaire 12-item short-form.

^d^BPI: Brief Pain Inventory.

^e^Picker Patient: Picker Patient Experience Questionnaire.

^f^N/A: not applicable.

^g^IES-R: Impact of Events Scale-Revised.

^h^OPIOID: Postoperative Opioid and Pain Management Questionnaire.

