##### Power Analysis

Our primary endpoint is composite of health care utilization, defined as the total number of days spent at home within the first 30 days after surgery. Secondary endpoints include mean GAD-7 and PHQ-9, KCCQ-12, Picker Patient Experience Questionnaire, IES-R, and Brief Pain Inventory Scores and mean inpatient and outpatient opioid use.

We will compare mean days with a two-tailed *t* test and set the power of this study at 80% with alpha (Type I error) of .05 and the Cohen *d* effect size (defined as the difference in means divided by standard deviation) between medium (0.5) and large (0.8) [69,70], which yields a minimum sample size of 52 patients to detect a large effect size and 128 to detect a medium effect size [71]. Incorporating 20% missingness, a sample size of 154 patients will adequately detect a medium effect size. We next verified this statistically derived sample size with clinically relevant examples. Although most large series reporting opioid use report the median and interquartile range of OME [47,72], our sample size should be sufficient to satisfy the central limit theorem and use mean values. At our institution, the mean opioid use after sternotomy in 2017 was 200 OMEs. We estimated that to detect a 30% reduction in opioid use (mean 140 OMEs) with a standard deviation of 125 OME in the control and 100 OME in the intervention arms, a sample size of 114 would be required. For composite health care utilization, demonstrating a 3-day difference between the arms with a 6-day standard deviation would detect by a total sample size of 128 patients. With 154 patients, we should have adequate power to detect a difference in our primary outcomes for aims 1 and 2.

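### GAD-7, PHQ-9 and KCCQ-12 are analysed without adjustment for the preoperative score, which for GAD-7 and PHQ-9 is instead one of the four outcome times; the cost is lost power on secondary endpoints

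*Protocol article*

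**What the plan says.** Under Aim 1, GAD-7 and PHQ-9 are administered "at 4 points: preoperative clinic visit, discharge, and at 30- and 90-day follow-up", so one time is preoperative and three are postoperative. Table 1 shows the same schedule.

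Aim 1, Analytic Approach, then gives three analyses:

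- Per-visit tests: "Mean total GAD-7 and PHQ-9 scores at each of the 4 time-points (Table 1) will be compared between the 2 groups", by two-tailed t test.
- A longitudinal test: "repeated measures ANOVA (analysis of variance) tests will be performed for the GAD-7 and PHQ-9 across the 4 time-points to examine differences between groups". The section does not say whether the term of interest is group or group-by-time.
- For function: "The mean intrapatient difference between preoperative clinic and 30-day follow-up in functional status scores on the KCCQ-12 will be evaluated" and compared between arms, with 5 points taken as clinically important.

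None of the three is described as adjusting for the preoperative score. Power Analysis ranks all three scales as secondary: "Secondary endpoints include mean GAD-7 and PHQ-9, KCCQ-12".

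**The concern.** The intervention cannot have had its postoperative effect at the preoperative visit. A group main effect taken over all four visits therefore averages the effect with one visit where it should be about zero, and the estimate shrinks. The t test at the preoperative visit says nothing about postoperative benefit. The postoperative t tests and the KCCQ-12 change score are valid comparisons, but they use the preoperative measurement either not at all or inefficiently.

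Anxiety, depression and function are central to Aim 1. At stake is a real effect going undetected when the same data, analysed with baseline adjustment, would have had a good chance of showing it. This is a loss of power; it does not inflate type I error.

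**Working it through.** **The plan's own figure.** Power Analysis says to "set the power of this study at 80% with alpha (Type I error) of .05", two-tailed. A noncentral-t calculation gives 128 in total for d = 0.5 and 52 for d = 0.8, exactly as stated. The same method is used below.

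**Inputs.**

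- From the protocol: two-sided alpha 0.05, 154 patients and 20% missingness. 154 × 0.8 = 123.2, so about 61.5 per arm.
- Assumed, because the protocol gives no value: 1:1 allocation, equal SDs (set to 1), compound symmetry with within-patient correlation r = 0.3, 0.5 or 0.7, no effect at the preoperative visit, and a constant postoperative effect d = 0.35.

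**Formulas.**

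- Group main effect over 4 visits: effect 0.75d (three visits at d and one at 0, divided by 4), variance (1+3r)/4.
- Baseline-adjusted mean of the 3 postoperative visits: effect d, variance (1+2r)/3 − r².
- Group-by-time: F test on 3 df with noncentrality (n/2)(0.75d²)/(1−r), n per arm.
- One visit: variance 1 unadjusted, 1−r² by ANCOVA, 2(1−r) as change.

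**GAD-7 and PHQ-9, d = 0.35.** The main effect estimates 0.75 × 0.35 = 0.2625.

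| | r = 0.3 | r = 0.5 | r = 0.7 |
|---|---|---|---|
| Variance, 4-visit main effect | 0.475 | 0.625 | 0.775 |
| Variance, adjusted 3-visit mean | 0.443 | 0.417 | 0.310 |
| Power, 4-visit main effect | 55% | 45% | 38% |
| Power, group-by-time | 36% | 49% | 73% |
| Power, adjusted 3-visit mean | 82% | 85% | 93% |
| Power, one visit, unadjusted t test | 49% | 49% | 49% |
| Power, one visit, adjusted | 52% | 60% | 77% |

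**At the protocol's medium effect, d = 0.5, 64 per arm.** The main effect estimates 0.375, with power 86/76/67%. Group-by-time, by simulation (4000 runs), has 67/84/98%. The unadjusted mean of the three postoperative visits has 97/93/88%, and the adjusted mean 99/99/>99%. In this case most of the loss against the main-effect reading comes from averaging in the preoperative visit. Baseline adjustment adds the rest.

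**KCCQ-12, one follow-up visit.** The variance of the change score relative to ANCOVA is 2(1−r)/(1−r²) = 2/(1+r) = 1.54/1.33/1.18. At d = 0.5 and 64 per arm, power is 66/80/95% for change, 84/90/98% for ANCOVA, and 80% for the 30-day score alone. Below r = 0.5 the change score does worse than ignoring the baseline.

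**The case against.** Several points for the plan stand.

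- **The dilution is conditional.** The protocol does not name the tested term. The 25% shrinkage belongs to the group main effect, which is the plain reading of a test of group differences. With arms equal at baseline, group-by-time is a legitimate, if omnibus, test of the treatment effect. At r = 0.7 it has about 73% power, nearly twice that of the main effect. It is still below the adjusted contrast in every case computed.
- **The large power gap belongs to one contrast.** The 82/85/93% applies to the difference averaged over three visits. For differences at a single visit, the gain over the planned t test is only about 4/12/28 percentage points.
- **KCCQ-12.** A reader might infer that the raw change also dilutes the effect or discards the baseline. It does neither: it is unbiased under randomization and uses the baseline, only less efficiently. The 5-point threshold is applied to a change, so reporting change is reasonable.
- **Missing surveys.** A reader might infer that every patient who misses one of the four surveys will be dropped. The document does not establish this. Patient Enrollment and Randomization provides for multiple imputation. Its wording refers to missed intervention points and says that patients lost to follow-up are censored, so whether it covers missed surveys is unclear.
- **The baseline may not be clean.** Randomization and the first coach contact take place at the same clinic visit as the preoperative questionnaires. The text does not give their order, and the Figure 2 image is not shown. Adjusting for a score taken after coaching began could remove part of the effect.

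The primary endpoint and its sample size are untouched.

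**Conclusion.** The point holds as a matter of efficiency on secondary endpoints. Under the stated assumptions, the planned longitudinal test of GAD-7 and PHQ-9 has 55/45/38% power (group) or 36/49/73% (group-by-time), against 82/85/93% for an adjusted contrast averaged over the postoperative visits. For KCCQ-12, the change score carries 18% to 54% more variance than ANCOVA.

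The adjusted analysis did better at every correlation tried. The size is less certain: the correlations, equal SDs, compound symmetry and a constant effect through 90 days are assumptions. The document supports no claim of bias in the KCCQ-12 comparison, of type I error inflation, or of harm to the primary analysis. The change is worth making before the data are analysed.

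**What to change.** - Analyse the discharge, 30-day and 90-day GAD-7 and PHQ-9 scores by a mixed model with preoperative score, arm, time and arm-by-time, using all available data. Name the arm difference averaged over the three postoperative visits as the main contrast, and also report the difference at each visit.
- Analyse 30-day KCCQ-12 by ANCOVA on its preoperative score. Keep the mean change against the 5-point threshold as a descriptive result.
- Drop the between-arm tests at the preoperative visit.
- State the order of questionnaires, randomization and first coach contact at that visit. Use the preoperative score as covariate only where it was completed before both.

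The cost is revised analysis wording and a check of when the preoperative forms were completed. No new patients or measurements are needed. The article reports 144 of 154 patients enrolled, with collection and analysis still to be completed, so the change can be made before results are known.

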## Methods

### Overall Study Design

We will perform a prospective, double-armed, randomized, controlled trial of 154 cardiac surgical patients at a large academic center to assess whether nonpharmacological interventions by a trained comfort coach affect patient experience, opioid use, and health care utilization as compared with usual care. The individualized comfort coach interventions will be administered at 6 time-points: (1) at the preoperative clinic, (2) on the day of surgery, (3) at extubation, (4) at chest tube removal, (5) at hospital discharge, and (6) at the 30-day clinic follow-up.

This study has 3 specific aims: (1) assess the effect of a comfort coach on patient experience, (2) measure differences in inpatient and outpatient opioid use and postsurgical health care utilization, and (3) qualitatively evaluate the effectiveness of the comfort coach intervention. Toward aim 1, we will use validated survey metrics to capture anxiety and depression (preoperative clinic, discharge, 30-day follow-up, and 90-day follow-up), functional status (preoperative clinic and 30-day follow-up), surgery-related psychological stress (30-day follow-up), patient-reported in-hospital pain (discharge), and patient experience (30-day follow-up). Toward aim 2, we will compare inpatient and postdischarge opioid use and patient-reported outcomes, including pain scores and pain management practices between groups. In addition, the composite primary endpoint of the study will be recorded as the total number of days spent at home out of the first 30 after surgery, incorporating hospital length of stay, readmissions, number of days in an extended care facility, emergency room, urgent care, and unplanned doctor visits. Aim 3 will include semistructured interviews of patients in the intervention group to understand the role, impact, and acceptability of a comfort coach.

All requirements for conducting human subjects research at the University of Michigan have been met. The study protocol has been reviewed, and the University of Michigan Institutional Review Board has approved this trial (quantitative, HUM00161399, and qualitative, HUM00170502). This clinical trial has been registered at ClinicalTrials.gov (NCT04051021).

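### The preoperative GAD-7 and PHQ-9 scores are analysed as a fourth outcome visit and never as a baseline, which costs precision and, if the ANOVA group main effect is meant, shrinks the estimate

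*Protocol article*

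**What the plan says.** The Aim 1 section of the protocol article schedules both scales "at 4 points: preoperative clinic visit, discharge, and at 30- and 90-day follow-up". Table 1 shows the same four columns.

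The Aim 1 Analytic Approach then gives two layers of analysis:

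- **By visit.** "Mean total GAD-7 and PHQ-9 scores at each of the 4 time-points (Table 1) will be compared between the 2 groups", using two-tailed t tests. The same sentence compares the severity categories by chi-square.
- **Longitudinal.** "repeated measures ANOVA (analysis of variance) tests will be performed for the GAD-7 and PHQ-9 across the 4 time-points to examine differences between groups", allowing for within-patient correlation.

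No covariate adjustment or change score is given for either scale. In the same paragraph KCCQ-12 is handled differently: its result is each patient's difference between the preoperative clinic and day 30. The Power Analysis section lists GAD-7 and PHQ-9 as secondary endpoints. Days at home is the primary endpoint.

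**The concern.** The preoperative score can do one of two jobs. As a baseline, it removes between-patient variation from the follow-up comparison. As an outcome, it adds a visit at which randomized arms are expected to be equal. The article gives it only the second job, for two of the scales central to Aim 1. Three things follow:

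- A group effect averaged over four visits includes one visit with no expected difference.
- The discharge, day-30 and day-90 t tests leave the patient's own starting score unused, although it is collected.
- The preoperative between-arm test answers no question about the intervention.

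What is at stake is precision for anxiety and depression and, under one reading of the ANOVA, an estimate that understates the follow-up effect. Anxiety is the mediator in the article's conceptual model, so a weak analysis there matters for interpretation.

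**Working it through.** **The plan's own figure.** The Power Analysis section says "set the power of this study at 80% with alpha (Type I error) of .05" and obtains "a minimum sample size of 52 patients to detect a large effect size and 128 to detect a medium effect size". The noncentral t distribution reproduces this: at d = 0.5, 64 per arm (128 in total) gives 80.1% power; at d = 0.8, 26 per arm (52) gives 80.7%. The enrolled 154 is 128 × 1.2 = 153.6, rounded up.

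**Inputs.**
- From the article: four visits, one of them preoperative; two-sided 0.05; 154 patients; 20% missingness. 154 × 0.8 = 123.2, or about 62 per arm.
- Assumed: 1:1 allocation (ratio not stated); unit SD; equal correlation ρ between any two visits (not given, so ranged from 0.3 to 0.7); effect δ = 0.4 SD at each follow-up; no arm difference preoperatively.

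**Formulas** (n per arm; SE = √(2 × variance / n)).
- Group main effect over four levels: difference (0 + δ + δ + δ)/4 = 0.75δ; variance (1 + 3ρ)/4.
- Mean of the three follow-ups: difference δ; variance (1 + 2ρ)/3.
- The same, adjusted for the preoperative score: difference δ; variance (1 + 2ρ)/3 − ρ².
- Single visit: variance 1 unadjusted, 1 − ρ² adjusted.
- Group-by-time interaction: F on 3 and 3(2n − 2) = 366 df, noncentrality (n/2) Σ(δⱼ − δ̄)²/(1 − ρ).

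**Sustained effect, δ = 0.4, n = 62, ρ = 0.5.**
- Four-level group effect: 0.30 / √(2 × 0.625 / 62) = 0.30 / 0.142 = 2.11; power 55%.
- Interaction: noncentrality 31 × 0.12 / 0.5 = 7.44; power 61%.
- Three follow-ups, unadjusted: 0.40 / 0.147 = 2.73; power 77%.
- Three follow-ups, adjusted: 0.40 / 0.116 = 3.45; power 93%.
- Single visit: 0.40 / 0.180 = 2.23, power 60% unadjusted; 0.40 / 0.156 = 2.57, power 72% adjusted.

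**Range over the assumed correlation** (δ = 0.4, n = 62).

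| ρ | Four-level group effect | Interaction, 3 df | Three follow-ups, unadjusted | Three follow-ups, adjusted |
|---|---|---|---|---|
| 0.3 | 67% | 46% | 86% | 91% |
| 0.5 | 55% | 61% | 77% | 93% |
| 0.7 | 47% | 85% | 70% | 98% |

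**At the plan's own values** (δ = 0.5, 64 per arm; ρ = 0.3, 0.5, 0.7). The four-level group effect has 86%, 76% and 67% power, the interaction 68%, 84% and 97%, and the adjusted three-visit mean about 99% or more throughout. A single-visit test at ρ = 0.5 has 80% unadjusted and 90% adjusted.

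**Fading effect** (n = 62, ρ = 0.5; effects at discharge, day 30, day 90).

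| Effects | Four-level group effect | Interaction, 3 df | Adjusted three-visit mean |
|---|---|---|---|
| 0.5, 0.25, 0 | 26% | 79% | 57% |
| 0.4, 0.4, 0 | 29% | 75% | 63% |
| 0.5, 0, 0 | 14% | 82% | 30% |

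A joint 3-df test of the three baseline-adjusted differences has noncentrality (n/2) δ′Σ⁻¹δ, where Σ has 1 − ρ² = 0.75 on the diagonal and ρ − ρ² = 0.25 off it. For 0.5, 0.25, 0 this is 31 × 0.40 = 12.4, or 84% power on 3 and 119 df. For a sustained 0.4 it is 31 × 0.384 = 11.9, or 82%.

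**The case against.** The tempting stronger reading is that the longitudinal estimate is biased toward zero by construction, so that a real effect would be reported as none. The article does not support this, for several reasons.

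- **The ANOVA term is not named.** Group-by-time is a standard treatment test in a pre/post repeated measures design. There the preoperative level acts as a reference, and nothing is diluted by a quarter. The choice of term may also sit in an analysis plan that is not shown. This stands: the 0.75 factor is conditional on the main-effect reading.
- **The ANOVA is supplementary.** The follow-up t tests are undiluted and unbiased, and could show an effect that the ANOVA main effect missed. This stands; their cost is precision only.
- **Two changes are mixed in 55% against 93%.** Dropping the preoperative level alone gives 77%; adjustment supplies the other 16 points. This stands.
- **A single averaged contrast is not always best.** Coach contact ends at the 30-day visit, so an effect that fades by day 90 is plausible. The interaction then beats the adjusted average (79% against 57% for 0.5, 0.25, 0). This stands, and the fix allows for it.
- **The preoperative test does no harm.** It is redundant and biases no treatment estimate. This stands.
- **The preoperative score may not be free of treatment.** Randomization and the first coach contact occur at the same clinic visit. The readable text does not give the order of survey and contact, and Figure 2, which may show it, is not available. If the survey came after contact, the dilution would be smaller.

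None of this answers the core point: the article names the tests and the visits, and uses the preoperative score as a baseline for KCCQ-12 but not for these two scales.

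**Conclusion.** The concern holds in a limited form. The stated analysis makes the preoperative GAD-7 and PHQ-9 an outcome and gives up the baseline information they carry. For a single follow-up visit this costs about 12 points of power (60% against 72%). Under the main-effect reading, the ANOVA also returns three quarters of a constant follow-up effect, with 55% power against 93% for the adjusted follow-up mean. Under the interaction reading there is no dilution, but power for a sustained effect is still lower (61%).

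The power figures rest on an assumed 0.4 SD effect, 62 per arm and ρ = 0.5. The 0.75 factor does not depend on ρ, but it needs a constant follow-up effect and a preoperative score untouched by the coach. The advantage of the adjusted average over the interaction needs a sustained effect. Type I error is not inflated, and days at home is unaffected. This is a worthwhile improvement to two secondary endpoints and does not threaten the trial's main conclusion.

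**What to change.** 1. Analyse the discharge, day-30 and day-90 scores as the outcomes, in a longitudinal model with visit, arm, arm-by-visit and the preoperative score as covariate.
2. Report the baseline-adjusted arm difference at each of the three visits.
3. Name the group test in advance. The average over follow-ups is strongest for a sustained effect; a joint or per-visit test is stronger if the effect fades by day 90.
4. Show the preoperative scores and severity categories descriptively by arm, without a between-arm test.
5. Use the preoperative score as baseline only where it was taken before the first coach contact, and state that order in the text.

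The cost is analysis wording; the scores are already scheduled for collection. The one small downside is that a rule is needed for patients without a usable preoperative score.
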